### Participant timeline {13}

See the participant timeline in Table 3.

**Table 3 Tab3:** During the study, laboratory tests and other complementary tests will be performed according to the clinical criteria of the physician in charge. (1) According to medical criteria. (2) This visit will be conducted by phone call or face-to-face if the physician in charge deems necessary. (3) Before administering treatment. (4) Fever in hospitalized patients with SARS-CoV-2 pneumonia is usually measured on the forehead with an infrared thermometer every 6 h or on demand, if the patient’s status so requires. (5) Fever in patients hospitalized for SARS-CoV-2 pneumonia, generally, is taken on the forehead with an infrared thermometer every 6-8 hours or on demand if the patient’s status so requires. Respiratory parameters: O2 saturation and respiratory rate. (6) Includes complete cell blood count, D-dimer, sedimentation rate, AST, ALT, bilirubin, creatinine, creatinine clearance, LDH, PT, aPTT, fibrinogen, ferritin, HDL, LDL, triglycerides, troponin, creatine-kinase, PCR, complement factor C4, C1 inhibitor antigen, and C1 inhibitor functional activity

		Visit 1	Visit 2	Visit 3	Visit 4	Visit 5	Visit 6	Visit 7 ^**(2)**^
	Patient screening	Treatment start	Hospitalization			Efficacy assessment	Hospital discharge	Study end
**Days of treatment**		**Day 1**	**Day 2**	**Day 3 (last dose)**				
**Days since the beginning of treatment administration**		**Day 0**	**Day 1**	**Day 2**	**Day 3**	**Day 10 (±1)**		**Day 28 (±3) from hospital discharge**
**Obtaining informed consent**	✔							
**Eligibility criteria assessment**	✔							
**Demographic data**	✔							
**Acute illness information (SARS-CoV-2 pneumonia):**	✔					✔		
**▫ New-onset radiological infiltrates** ^**(4)**^								

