### Study procedure

Patients will be screened at the emergency department of each hospital or on the hospitalization ward on day 1 of admission. Patients enrolled on the study will be followed up until 28 days (1 month) from hospital discharge.

At the *baseline visit* (day 0, patient screening), a complete evaluation to confirm that the patient meets all the inclusion criteria and none of the exclusion criteria will be carried out. Every patient will be informed about the study and will be given the information sheet and informed consent to sign prior to enrollment in the clinical trial. Demographic parameters, medical history, information on concomitant medication, and the presence of adverse events will be recorded.

At *visit 1* (treatment start visit), a new clinical assessment will be performed. Patients will be re-evaluated to confirm (double-check) that they meet all the inclusion criteria and none of the exclusion criteria. Patients will be randomized and assigned to one of the treatment arms. Treatment will then be started. One dose of icatibant will be given every 8 h for 3 days, for a total of 9 doses, for patients assigned to the experimental group, along with SoC.

Baseline visit and visit 1 may overlap. If this occurs, the investigator will collect all the information from both visits in the electronic case report form (e-CRF).

During hospital admission (number of days may vary by length of hospital admission), all outcomes related to the patient’s clinical status and clinical severity assessment criteria will be collected daily from the medical records. All medication received by patients, as well as fluid therapy and the presence of adverse events, will also be recorded.

The following information will be retrieved until day 4 of hospitalization: general examination, vital signs (including SpO_2_), clinical data for study outcomes and adverse events assessment, 12-lead EKG, and laboratory analysis (including renal function, hepatic enzymes, and parameters suggestive of ischemia—creatine kinase, troponin). Serious adverse events (SAEs) and all any AEs will be collected, even if they are not part of the study’s endpoints or related with the investigational drug.

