*Visits 2* and *3* will correspond to safety assessment during hospital admission. Visit 2 and visit 3 will take place, respectively, on day 2 (24 h after treatment start, before the 4th dose of icatibant) and on day 3 (48 h after treatment start, before the 7th dose of icatibant). *Visit 4* will take place 72 h after treatment start, end of treatment’ visit (after all doses are administered). Hospital discharge may occur after completing visit 4, if the patient is clinically stable (i.e., no fever for 48 consecutive hours without antipyretic medication, PaO_2_/FiO_2_ > 380 or O_2_ saturation > 94%, respiratory rate ≤ 24 bpm, absence of decompensation of any comorbidity).

*Visit 5* [10 (± 1) days after treatment start] will be an efficacy assessment visit. A clinical assessment will be performed and the patient’s clinical status and clinical stability criteria^#^, as well as the medication used and the presence of adverse events, will be reevaluated. If hospital discharge visit overlaps with the day 10 visit, the investigator will only complete the day 10 visit in the e-CRF, clarifying that it is also the hospital discharge visit. The patient will be sent home and will be informed of the confinement regimen measures to be followed at home (or similar, e.g., medicalized hotel), if necessary.

A patient classified as a treatment failure (i.e., non-responder—any patients who do not meet the criteria to be considered a responder) will have their participation in this study terminated. Afterwards, their condition will be treated at the discretion of the physician in charge of their particular case.

^#^Clinical stability (defined as (1) body temperature ≤ 37.5 °C for 48 h without any antipyretic medication, (2) PO_2_/FiO_2_ > 380 or oxygen saturation > 94%, (3) respiratory rate ≤ 24 rpm, and (4) the absence of any kind of comorbidity decompensation) will also be assessed and the time to achieve it will be calculated starting from the time of the baseline visit.

If the patient is discharged before the 10th day since treatment start, the investigator must complete the day 10 visit in the e-CRF for the efficacy assessment on the same day as hospital discharge.

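### Clinical stability accepts oxygen saturation > 94% without requiring it off supplemental oxygen, so time to stability need not reflect respiratory recovery

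*Protocol article*

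**What the plan says.** The protocol article states the rule twice under Study procedure.

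- **Discharge after visit 4.** "Hospital discharge may occur after completing visit 4, if the patient is clinically stable". Stability is spelled out there as "no fever for 48 consecutive hours without antipyretic medication", a PaO2/FiO2 ratio above 380 or saturation above 94%, a respiratory rate of at most 24, and no decompensated comorbidity.
- **Visit 5 footnote.** Temperature must stay at or below 37.5 °C "for 48 h without any antipyretic medication". The oxygenation condition is a ratio above 380 or, joined by the word or, "oxygen saturation > 94%, (3) respiratory rate ≤ 24 rpm, and (4) the absence of any kind of comorbidity decompensation". Stability "will also be assessed and the time to achieve it will be calculated starting from the time of the baseline visit".

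The temperature condition is qualified by treatment in both places. The saturation condition is not qualified in either, and no other section of the article adds a room-air or FiO2 requirement.

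Under Eligibility criteria {10}, patients must be WHO grade 4 or 5 with a ratio below 380. By Table 1, that means low-flow oxygen (grade 4) or high-flow oxygen or non-invasive ventilation (grade 5).

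**The concern.** Saturation in a patient on oxygen reflects both the lungs and the treatment. The PaO2/FiO2 ratio corrects for the oxygen given; saturation alone does not. Because the two are alternatives, a patient whose oxygen keeps saturation above 94% meets the oxygenation condition whatever the ratio, possibly as early as baseline. The other three conditions still have to be met, but none of them measures oxygenation.

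Impaired oxygenation is what brings these patients into the trial. A time to stability that can be reached with the ratio still below the entry threshold does not reliably measure recovery from it.

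The trial's own instruments keep the two things apart. NEWS 2, as listed under Secondary outcomes, scores saturation and supplemental oxygen separately, and in Table 1 WHO grades 3 and 4 differ only by oxygen use.

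**Working it through.** The protocol gives no figure to reproduce here. The check is of the wording, followed by an illustration of how far the two oxygenation alternatives can disagree.

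**Inputs from the protocol article:** ratio above 380 or saturation above 94% (Study procedure); entry at WHO grade 4 or 5 with a ratio below 380 (Eligibility criteria {10}).

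**Assumptions, not in the protocol article:** FiO2 values of 0.24 to 0.60, and the Severinghaus dissociation curve, with p = PaO2 in mmHg:

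S(p) = 1 / (23400 / (p³ + 150p) + 1)

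**Step 1. PaO2 at a saturation of 95%.** At p = 75.7, p³ + 150p is about 445,000 and 23400/445,000 = 0.0526, so S = 1/1.0526 = 0.95.

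**Step 2. Ratio = 75.7 / FiO2,** with two sensitivity ranges: PaO2 shifted by ±20%, and a true saturation of 93% (p = 67.0) to 97% (p = 90.6), which allows an oximeter error of ±2 points.

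**Step 3. Saturation at which the ratio would reach 380.** PaO2 needed = 380 × FiO2, put back into S(p).

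| FiO2 | Ratio at 95% | PaO2 ±20% | True saturation 93–97% | PaO2 for ratio 380 | Saturation there |
|---|---|---|---|---|---|
| 0.24 | 315 | 252–378 | 279–377 | 91.2 | 97.1% |
| 0.28 | 270 | 216–324 | 239–323 | 106.4 | 98.1% |
| 0.40 | 189 | 151–227 | 168–226 | 152 | 99.3% |
| 0.60 | 126 | 101–151 | 112–151 | 228 | 99.8% |

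Every ratio in columns 2 to 4 is below 380, although the displayed 95% passes the saturation alternative. Readings from 95% up to the value in the last column pass on saturation and fail on the ratio. The two alternatives agree again at high saturation on little oxygen: 98% at FiO2 0.24 gives p = 104.2 and a ratio of 434.

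**Step 4. Room air.** 75.7/0.21 = 360. A ratio of 380 needs p = 79.8, which is a saturation of 95.7%. Off oxygen the two alternatives nearly coincide; on oxygen they separate, and the gap widens as FiO2 rises.

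**The case against.** **This is a condensed article, and room air was probably meant.** The near-agreement on room air does suggest that saturation was intended to stand in for the ratio when no arterial gas is available. But the article prints a complete four-part rule with cut-offs, twice, and each time qualifies fever by treatment while leaving saturation unqualified. Applied as written, the rule counts patients on oxygen. If room air was intended, the text does not say so, and one phrase would settle it.

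**No listed result depends on it.** This stands. Time to clinical stability is in none of the listed objectives or numbered outcomes. Oxygen use is captured elsewhere: by the WHO grade, by NEWS 2, and by safety outcome 16, which counts patients needing oxygen between discharge and visit 7.

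**A reader might infer that the primary outcome is biased,** because the same wording governs discharge and the clinical response needs WHO grade 2, 1 or 0. The article does not support that. The responder definition uses the WHO scale and the absence of grade 3 to 5 adverse events, not this rule. Discharge is permitted rather than required, so the physician still decides. The silence of grades 1 and 2 on home oxygen belongs to the WHO scale. A sensitivity analysis that recodes responders discharged on oxygen would examine that scale, not this definition, and is not called for here.

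**A reader might also object to the clock,** which runs from the baseline visit rather than from treatment start. Since "Baseline visit and visit 1 may overlap", the gap will often be nil, and nothing rests on it.

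**Recruitment is under way.** Under Trial status, 77 patients were already enrolled. Changing bedside discharge practice now would treat early and late patients differently. That argues for making the correction at analysis.

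**Conclusion.** The point holds as a minor defect in a stated definition. As written, a patient still on oxygen who meets the temperature, respiratory rate and comorbidity conditions counts as stable with a ratio that may be well below 380: about 126 to 315 at a saturation of 95% for FiO2 0.60 to 0.24, and 101 to 378 across the sensitivity ranges. These figures rest on the assumed curve and FiO2 values. The reading of the rule rests only on the printed text.

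The consequence is limited to the calculated time to clinical stability, an additional measure. The article does not give the share of patients who would be counted stable while on oxygen, so the shift in that measure, and any difference between arms, cannot be sized.

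**What to change.** In the visit 5 definition, count saturation above 94% only when it is measured without supplemental oxygen (on room air, or at the patient's pre-illness oxygen level). Leave the ratio alternative as it is, since it already accounts for FiO2.

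No new data item is needed in hospital, where "clinical status and clinical severity assessment criteria will be collected daily from the medical records". WHO grade 3 rather than 4 or 5, together with the NEWS 2 oxygen parameter, identifies days off oxygen. Derive the corrected date for all patients at analysis, so that those already enrolled and those still to come are treated alike. Align the discharge wording with the definition where the sponsor agrees.

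The cost is one phrase and one derivation rule. The downside is that stability will be reached later, and a patient who leaves hospital on new oxygen without a ratio above 380 will not have reached it by discharge.

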#### Secondary outcomes

Clinical secondary outcomes are as follows: (1) “long-term efficacy”: number (percentage) of patients who reached a sustained 48-h grade 2, grade 1, or grade 0 classification on the WHO 8-point ordinal scale for clinical status assessment 10 days after starting treatment and within 28 days after hospital discharge; (2) time to achieve a clinical response: time (days) between visit 1 (treatment start visit) and the day of recording sustained 48-h grade 2, grade 1, or grade 0 classification on the WHO 8-point ordinal scale for clinical status assessment; (3) time to achieve an afebrile state: time (days) to reach a 48-h sustained afebrile state (i.e., body temperature ≤ 37.5 °C) without antipyretic medication; (4) time from symptom onset: time (days) between the first COVID-19-related symptom and visit 1 (treatment start visit); (5) number (percentage) of patients considered as responders based on National Early Warning Score 2 (NEWS 2)*. Responder is defined as a patient who reaches at least a sustained 24-h score ≤ 2; and (6) COVID-19-related relapse: number (and percentage) of patients discharged who presents a COVID-19-related relapse or comorbidity.

*Clinical severity assessment will be carried out using the NEWS 2: https://www.mdcalc.com/national-early-warning-score-news-2 [16]. This score, accessed by electronic devices, has demonstrated the ability to determine the degree of illness of a patient and prompts critical care intervention. The score is based on 7 clinical parameters (respiratory rate, oxygen saturation, any supplemental oxygen requirement, temperature, systolic blood pressure, heart rate, level of consciousness [Alert, Responsive to voice, Responsive to pain, Unresponsive]).

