Safety secondary outcomes are as follows: (7) number (and percentage) of patients with any AEs; (8) number (and percentage) of AEs; (9) number (and percentage) of SAEs: according to their severity and relationship with treatment, and by determining the number of patients with a grade 3, grade 4, or grade 5 adverse event according to the CTCAE (Common Terminology Criteria for Adverse Events—see Table 2); (10) mortality for any cause: number (and percentage) of patients who died; (11) COVID-19-related mortality: number (and percentage) of patients who died due to COVID-19; (12) time until death: number of days from visit 1 until death; (13) COVID-19-related complications: number (and percentage) of patients who had any complications and number (and percentage) of complications up to 28 days after hospital discharge (visit 7); (14) number (and percentage) of patients who require intensive care; (15) number (and percentage) of patients requiring intensive care and invasive mechanical ventilation; (16) number (and percentage) of patients who require oxygen supplementation from hospital discharge up until visit 7; (17) number (and percentage) of patients diagnosed with another nosocomial infection; and (18) number (and percentage) of patients who requires hospital readmission within 28 (± 3) days from hospital discharge.

Safety assessment will be carried out from the treatment’s first dose up to 28 (±3) days after hospital discharge according to the CTCAE (all AEs, SAEs, and SUSARs will be reported in the e-CRF).

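### Time to clinical stability is counted from the screening visit, before randomisation, while the protocol's time to response and time until death are counted from visit 1

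*Protocol article*

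**What the plan says.** All places are in the protocol article.

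- **Study procedure, note defining clinical stability:** after listing the four stability conditions, the note says that "the time to achieve it will be calculated starting from the time of the baseline visit".
- **Study procedure, baseline visit:** this is the screening visit, at which eligibility is checked and consent obtained. It is labelled day 0.
- **Study procedure, visit 1:** after a fresh clinical assessment and a second eligibility check, "Patients will be randomized and assigned to one of the treatment arms. Treatment will then be started".
- **Study procedure, relation of the two visits:** "Baseline visit and visit 1 may overlap". Overlap is allowed, not required, and no longest permitted interval is given.
- **Secondary outcomes, item 2 (time to clinical response):** "time (days) between visit 1 (treatment start visit) and the day of recording" of the sustained response.
- **Secondary outcomes, item 12:** "time until death: number of days from visit 1 until death".

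**The concern.** A comparison of randomised arms should start its clock at randomisation. Time before that point is untreated in both arms and carries no information about icatibant. With the clock started at screening, two things follow whenever screening and visit 1 are apart:

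1. Each patient's time to stability includes the gap, so the absolute times are too long.
2. A patient who already meets the stability criteria before visit 1 is recorded as reaching stability in an arm to which he or she had not yet been assigned.

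The origin also departs from the one the protocol uses for its two numbered times with a stated follow-up origin, and no reason is given. This has some practical weight because the Sample size section says the results are meant to inform the planning of a later trial, for which clean absolute times are useful.

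**Working it through.** The protocol gives no figure for this measure, so there is nothing to reproduce. The check has two parts: the text, and a sense of scale.

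**1. Are the baseline visit and visit 1 the same event?**

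Study procedure describes them in separate paragraphs. Table 3 gives screening and visit 1 separate columns. The section on biological specimens lists blood samples at the baseline visit and, separately, at visit 1. No sentence equates the two. The day labels do point to a short gap: Study procedure calls the baseline visit day 0, and Table 3 calls visit 1 Day 0 since the start of treatment.

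**2. Can stability be reached before visit 1?**

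| Condition | At entry (Eligibility criteria) | For stability (Study procedure) |
|---|---|---|
| Oxygenation | PaO2/FiO2 < 380 | ratio > 380 **or** saturation > 94% |
| Temperature | no requirement | ≤ 37.5 °C for 48 h without antipyretics |
| Respiratory rate | no requirement | ≤ 24 |
| Comorbidity | no requirement for absence of decompensation | no decompensation |

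Because saturation alone can satisfy the oxygenation condition, a patient can be eligible and stable at the same time. The second eligibility check at visit 1 therefore does not rule this out. The 48-hour afebrile condition makes it uncommon: within a gap shorter than 48 h it can be met only if the afebrile run began before screening.

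**3. How large is the effect?**

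From the protocol: 60 patients per arm, and Cox regression among the methods named for secondary outcomes. Assumed, because the documents do not give them: exponential times, control median 6 days from visit 1, true hazard ratio (HR) for stability 1.5 or 1.0, censoring at day 28, mean gap 0 to 2 days (constant, or uniform from 0 to twice the mean), and 0 to 20% of patients already stable before visit 1. There were 2000 simulated trials per row. The early-stable patients are drawn at the same rate in both arms.

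| Gap (mean) | Already stable | True HR | HR, visit 1 / baseline origin | Rejection rate, visit 1 / baseline | Control median (days), visit 1 / baseline |
|---|---|---|---|---|---|
| constant, 1 day | 0% | 1.5 | 1.499 / 1.499 | 0.575 / 0.575 | 6.04 / 7.04 |
| variable, 2 days | 0% | 1.5 | 1.496 / 1.485 | 0.560 / 0.551 | 6.05 / 8.12 |
| variable, 1 day | 5% | 1.5 | 1.507 / 1.474 | 0.593 / 0.535 | 6.09 / 6.66 |
| variable, 1 day | 10% | 1.5 | 1.506 / 1.438 | 0.574 / 0.481 | 6.04 / 6.13 |
| variable, 2 days | 20% | 1.5 | 1.505 / 1.373 | 0.572 / 0.392 | 6.11 / 6.24 |
| variable, 1 day | 10% | 1.0 | 1.000 / 0.999 | 0.049 / 0.056 | 6.05 / 6.16 |
| variable, 2 days | 20% | 1.0 | 1.003 / 1.001 | 0.044 / 0.054 | 6.07 / 6.22 |

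Reading the table:

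- **Gap alone:** the median shifts by about the gap. The HR hardly moves, because adding the same amount to every time leaves the order of events unchanged.
- **Gap plus early-stable patients:** the HR is diluted, and the early events partly hide the lengthening of the median.
- **No treatment effect:** the HR stays at about 1 and the rejection rate near 0.05.

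**4. What would the fix recover?**

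The visit 1 columns keep all 120 patients at risk. If early-stable patients were instead left out, fewer patients would remain, so the rejection rate would not return fully to those columns. An approximation is power = Φ(ln(HR) × √d / 2 − 1.96), where d is the number of events. The share with an event by day 28 is 1 − 2^(−28/6) = 0.961 for control and 1 − 2^(−28×1.5/6) = 0.992 for icatibant, mean 0.976.

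- All 120: d = 117.2, and 0.4055 × √117.2 / 2 = 2.194, so power = Φ(0.234) = 0.59. This agrees with the simulated 0.55 to 0.60.
- 10% left out (108): d = 105.5, statistic 2.082, power = Φ(0.122) = 0.55, against 0.48 with the baseline origin.
- 20% left out (96): d = 93.7, statistic 1.963, power = Φ(0.003) = 0.50, against 0.39.

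**The case against.** The strongest reply is that this is a loosely worded note about a measure that hardly matters.

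- **The gap may be close to zero.** Both visits carry the label day 0. Screening is on the first day of admission, the Recruitment section places inclusion and randomisation in the emergency department, and icatibant is to be prepared directly after randomisation. This stands as a limit on size. It does not remove the point, because no maximum gap is written and the visits are described separately.
- **Early stability should be rare.** The 48-hour afebrile condition supports this. The 5 to 20% shares above are assumptions, and nothing in the documents supports any particular value.
- **The measure is not a listed outcome.** Correct: time to clinical stability appears neither in the objectives nor among outcomes 1 to 18, and no between-arm analysis of it is spelled out. The primary outcome is untouched.

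A reader might go further and infer that the earlier origin by itself pulls the treatment contrast towards no effect. One could argue this from medians: 5 against 4 days from visit 1 is a ratio of 1.25, and with a 1-day gap it becomes 6/5 = 1.20. The documents do not support that inference. A ratio of medians is not a planned measure, the difference stays at 1 day in the same example, and the HR is essentially unchanged by a gap alone. Nor does anything suggest an advantage to one arm, since the interval precedes allocation.

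An unseen analysis plan is not a full answer either. The protocol does not leave the origin open: it states one, and it differs from its own convention.

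**Conclusion.** The inconsistency is real and minor. The stability clock starts at screening, whereas time to response and time until death start at visit 1, when patients are randomised. Where the visits are apart, absolute times are too long by the gap, and patients already stable before visit 1 count as events in their assigned arm.

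The size depends on two quantities the documents do not give. If the visits coincide there is no effect. With a gap alone, medians rise by about the gap and the HR barely changes. Only if some patients are already stable before visit 1 is the HR diluted: under the stated assumptions from about 1.5 to 1.47 at 5%, 1.44 at 10% and 1.37 at 20% with a 2-day mean gap. Under no effect there is no bias and no material rise in false positives. No numbered outcome is affected, so this is a desirable correction rather than a necessary one.

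**What to change.** In the note on clinical stability under Study procedure, replace the baseline visit with visit 1 (randomisation) as the time origin, matching outcomes 2 and 12.

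Add one sentence on patients who already meet all the stability criteria at visit 1. Any rule will do if it is fixed in advance and applied identically in both arms. For example, they could be treated as not at risk for this measure, with their number reported by arm.

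The cost is one phrase and one sentence. No new data are needed: status is assessed at visit 1 and then collected daily from the records during admission. For patients already enrolled, the times can be recalculated from the recorded date of visit 1.
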